**Methods:**

Thirty-nine patients will be assessed at baseline (T0–18 h of coma) and randomly assigned to the PM (control group), BFRp, or BFRpE groups. The training protocol will be applied in both legs alternately, twice a day with a 4-h interval until coma awake, death, or ICU discharge. Cardiovascular safety and applicability will be evaluated at the first training session (T1). At T0 and 12 h after the last session (T2), muscle thickness and quality will be assessed. Global muscle strength and physical function will be assessed 12 h after T2 and ICU and hospital discharge for those who wake up from coma. Six and 12 months after hospital discharge, physical function and quality of life will be re-assessed.

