##### Cardiovascular safety and applicability of peripheral muscle training

To assess cardiovascular safety, HR values < 50 bpm or > 180 bpm, SBP < 80 mmHg or > 160 mmHg, DBP < 60 mmHg or > 80 mmHg, MAP < 60 mmHg or > 120 mmHg, cardiac or respiratory arrythmias, SpO_2_ < 88%, signals of respiratory discomfort [50, 51], or signals of deep venous thrombosis will be considered criteria to interrupt the protocol. Except for the occurrence of deep venous thrombosis, two consecutive training attempts will be performed after the first training interruption before withdrawing the patient from the study. It is suggested for two main reasons: to exclude the possibility of an occasional adverse event due to the variability of the clinical conditions, and to maintain the training frequency in case the patient continues in the study. In case of exclusion, the protocol will be considered unsafe for this patient. However, in case 15% or more unsafe conditions occur in the same training protocol, the protocol will be excluded from the study. To evaluate the applicability, the number of adverse events and intercurrence will be recorded, and if a total number of adverse events and/or intercurrence overcome 20% of the total training sessions, or there is deep venous thrombosis occurrence in at least 5% of the patients, protocols will be considered unsafe and impracticable. If cardiovascular variations are greater than 20% of the baseline, the protocol will be considered impractical.

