#### Measurement of secondary outcomes

##### Neuromuscular adaptations of muscle mass and strength

Muscle mass and quality adaptations will be assessed daily prior to the first training session (~ 12 h from the last session) and 12 h after the last training session (T2) (until 12 h prior to the coma awakening), to the predicted death or ICU discharge. The muscle mass of the VL, *rectus femoris* (RF), and anterior tibial (AT) will be measured by MT and muscle quality, by echo intensity, both analyses obtained by ultrasound images. If the patient awakes from a coma and has the appropriate cognition to collaborate in active assessments, the global muscle strength will be evaluated by the Medical Research Council (MRC) score after 12 h of T2, in the ICU and at hospital discharge. Adequate cognition will be assessed by the absence of delirium after completing the Confusion Assessment Method for Intensive Care Units (CAM-ICU) score [52].

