### Quality of life assessment

#### Quality of life using the SF-36 questionnaire

Quality of life will be assessed using the SF-36 questionnaire, an instrument of good acceptance, reliability, and validity for ICU patients validated in Brazil and easily administered by telephone [45, 46, 53, 54]. It comprises 8 domains: physical function, role-physical, bodily pain, general health, vitality, social functioning, role-emotional, and mental health. Scores range from 0 to 100, where 0 corresponds to the worst general health status, and 100 corresponds to the best health condition [86–88]. The categorization and description of the methods and analyses are shown in Table 2.

**Table 2 Tab2:** Categorization and description of the methods and analyses of the study variables

Evaluation category	Organic responses	Method of evaluation	Variables in analyses
Safety and applicability	Acute cardiovascular	Pulse wave analysis (PWA)	MAP, SBPc, SBPp, DBPc, and DBPp (mmHg)
Safety and applicability	Acute cardiovascular	Analyses of the vital signs	HR (bpm) and SpO_2_ (%)
Muscle systems	Muscle mass adaptation	Ultrasound image	Muscle thickness (cm)
Muscle systems	Muscle quality adaptation	Ultrasound image	Echo intensity (A. U. from 0 to 256)
Neuromuscular systems	Global muscle strength adaptations	Medical Research Council (MRC) Score	Number scoring (0 to 60)
Physical function	Adaptations in physical function in ICU	Physical Function in the Intensive Care Test Scored (PFIT)	Number scoring (0 to 12)
Physical function	Adaptations in physical functional performance after hospital discharge	Performance in the basic activities of daily living by the Barthel Index (BI) by telephone interview	Number scoring (0 to 100)
Clinical outcomes	Adaptations in quality of life	Medical Outcome Study 36 – Item Short Form Health Survey (SF-36) questionnaire	Number scoring (0 to 100)

*SBPc* central systolic blood pressure, *SBPp* peripheral systolic blood pressure, *DBPc* central diastolic blood pressure, *DBPp* peripheral diastolic blood pressure, HR heart rate, *MAP* mean arterial pressure, *SpO*_*2*_ peripheral oxygen saturation, *ICU* intensive care unit

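### The 5% thrombosis limit relies on signs that interrupt training in comatose patients; silent or later events are not assured of being counted, and the denominator is not stated

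*Protocol article*

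**What the plan says.** The section on cardiovascular safety and applicability of peripheral muscle training in the Protocol article mentions thrombosis in two roles. First, it is a reason to stop: "signals of deep venous thrombosis will be considered criteria to interrupt the protocol". Second, it is a decision limit: if "there is deep venous thrombosis occurrence in at least 5% of the patients, protocols will be considered unsafe and impracticable". An alternative trigger for the same label is "if a total number of adverse events and/or intercurrence overcome 20% of the total training sessions". The section also says that "the number of adverse events and intercurrence will be recorded", without a method or period specific to thrombosis.

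The abstract (Methods) gives the timing: "Cardiovascular safety and applicability will be evaluated at the first training session (T1".

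The other measurements described serve other purposes:
- Table 2 lists pulse wave analysis and "Analyses of the vital signs" under safety and applicability.
- Ultrasound is for muscle thickness and echo intensity ("both analyses obtained by ultrasound images").
- The Doppler probe is placed on the posterior tibial artery to set the cuff pressure.
- The calls at 6 and 12 months cover the Barthel Index and the SF-36.

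Table 1 admits patients at RASS -5 or -4, or Glasgow 3 to 5, with a predicted coma of 2 to 6 days.

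**The concern.** The limit needs a count of patients in whom thrombosis occurred. The only recognition route that the article states belongs to the stopping rule for a session. That route is narrow in two ways. Patients at this depth of coma cannot report pain or tenderness, which leaves only what an observer can see. And an interruption criterion works only while sessions are being given, whereas survivors are assessed again at hospital discharge and later.

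The stated windows also disagree. The abstract puts the evaluation at T1, but a limit expressed as a share of all training sessions can be computed only over the whole training period.

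Cardiovascular safety and applicability are the primary objectives, and repeated cuff compression is the exposure under test. An under-count would make a protocol look better on a primary objective, and the data are meant to inform a later trial.

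**Working it through.** **Inputs**
- Total sample: 39 (Sample size rationale). Equal allocation to three arms is assumed, giving 13 per arm. The article starts from 30 and allows 10% loss, but 30/0.90 = 33.3, so 34; 39 would allow 1 − 30/39 = 23% loss. That mismatch is a separate matter, and 39 is used here as stated.
- Limit: 5% of patients. No derivation is given, so there is nothing to reproduce. The denominator is not stated, so both readings are shown.
- True risk p and share of thromboses recognised s: neither is in the document. Both are assumptions, shown as ranges.

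**Step 1. What the limit means in patients.** Per arm, 1/13 = 7.7%, so below 5% can only mean zero events. Over all 39, 1/39 = 2.6% passes and 2/39 = 5.1% does not.

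**Step 2. What a passing count rules out.** For 0/13 the one-sided 95% upper limit is 1 − 0.05^(1/13) = 20.6% (24.7% as the upper end of a two-sided interval). If only a share s is recognised, the limit for the true risk is 0.206/s: 41% at s = 0.5 and 82% at s = 0.25. With the base of 10 per arm, 0/10 gives 1 − 0.05^(1/10) = 25.9%. Pooled, 1/39 has an exact one-sided upper limit of 11.6%, or 23% at s = 0.5.

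**Step 3. Chance of staying below 5%.** Let q = p × s. Per arm the chance is (1 − q)^13. Pooled it is (1 − q)^39 + 39q(1 − q)^38.

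| True risk p | Basis | s = 1 | s = 0.5 | s = 0.25 |
|---|---|---|---|---|
| 10% | arm of 13 | 0.25 | 0.51 | 0.72 |
| 10% | all 39 | 0.09 | 0.41 | 0.75 |
| 20% | arm of 13 | 0.055 | 0.25 | 0.51 |
| 20% | all 39 | 0.002 | 0.09 | 0.41 |

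At a true risk of twice the limit, moving from full to half recognition roughly doubles the chance that an arm passes (0.25 to 0.51).

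**Step 4. Sample size needed.** For zero events to put the one-sided 95% upper limit below 5%, n must exceed ln 0.05 / ln 0.95 = 58.4, so 59 per protocol. Better detection alone cannot make a passing result conclusive at 13 per arm.

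**The case against.** Several stronger readings are tempting, and the document does not support them.

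- *Later thromboses are excluded.* A reader might infer this by carrying the interruption criterion over to the 5% rule. That rule is worded as occurrence, and adverse events are recorded generally, so an event diagnosed after the last session could fit. The text is silent on the window; it does not exclude such events.
- *The plan treats a rate below 5% as proof of safety.* It does not say so. It says only when protocols are to be called unsafe. The binary label and the hypothesis of no negative cardiovascular effects invite the inverse conclusion, but it remains an inference.
- *Thrombosis alone has its own arm-level limit.* It does not. The limit stated per protocol is the 15% rule for unsafe conditions, and cardiovascular variation above 20% of baseline has a limit too.
- *Coma makes signs useless.* It removes symptoms, not observable signs. The Table 1 criteria are also rechecked before each session, which might catch an overt case, although no thrombosis test is named.

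Two further objections carry weight. Table 2 is weak evidence on its own, because arrhythmias and adverse events are absent from it too although the text uses or records them. And a condensed article may leave the method of confirmation to a full protocol. The point therefore does not rest on a missing test. It rests on what the article does state: a decision limit, a sign-based criterion, and two evaluation windows that do not agree.

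Finally, much of the imprecision is due to pilot size. That is correct: 20.6% holds with perfect detection. Incomplete recognition adds to it, always in the direction of a pass.

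**Conclusion.** The concern holds in limited form. Thrombosis is one of two sufficient triggers for the unsafe label. Its only stated recognition route is signs that stop a session in patients who cannot report symptoms, and the abstract and Methods disagree on when safety is evaluated. Silent or later events are not assured of being counted, and the denominator is open.

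Applied per arm with equal allocation, passing means 0/13. That is compatible with a true risk of up to 20.6% with perfect detection, about four times the limit, and 41% at an assumed 50% recognition. Pooled over 39, the corresponding limits for one event are 11.6% and 23%. The 50% and 25% recognition shares and the 10% and 20% true risks are illustrative. That a count below the limit is weak evidence of safety does not depend on them.

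**What to change.** 1. Reconcile the abstract and the safety section on the period over which safety and applicability are evaluated.
2. Count every deep venous thrombosis or pulmonary embolism diagnosed in routine care from randomisation to hospital discharge. Take it from the hospital record and report it by randomised arm, whether or not it interrupted a session.
3. State the denominator of the 5% rule, and that the rule applies to clinically recognised thrombosis.
4. Report the count per arm with its exact upper confidence limit.
5. State that a count below the limit does not establish thrombotic safety.

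The cost is a record review for 39 patients, a few sentences of wording, and a weaker safety claim. No new imaging is added and no threshold or stopping rule is altered. Record review will not find silent thromboses, nor events first diagnosed after hospital discharge. Both should be acknowledged as limitations.

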### Secondary objective

The secondary objective is to investigate the effects of this intervention on neuromuscular adaptations, physical function, and quality of life of ICU coma-surviving patients.

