### Study population

The inclusion, non-inclusion, and exclusion criteria are shown in Table 1. All the criteria will be reevaluated before each training session, according to the clinical specificity of the criteria (Table 1). All non-included patients will be re-evaluated after 18 h of coma, except for patients whose hospitalization is longer than 18 h prior to ICU admission. In conclusion, all patients will be assisted by the ICU physiotherapy team. Additionally, the number of PM sessions or any type of physical therapy intervention in the peripheral muscle will be quantified to control the total volume of stimulus for each patient.

**Table 1 Tab1:** Inclusion, non-inclusion, and exclusion criteria of the study population

Inclusion criteria	Non-inclusion criteria	Exclusion criteria
1. Age of 25 to 55 years	1. Persistent arrhythmia with atrial fibrillation	1. Obese (BMI > 30 kg/m^2^)
2. Scores − 5 or − 4 according to the Richmond Agitation-Sedation Scale (RASS) or 3 to 5 in the Glasgow Comatose Scale	2. Pre-existing atrioventricular block or ventricular tachycardia	2. More than one thromboembolism risk factor
3. Maximal 18 h of coma in ICU admission or during critical care hospitalization	3. Recent acute myocardium infarction	3. Previous venous thrombosis and/or pulmonary embolism
4. Prediction of coma length between 2 and 6 days	4. Provisional or definitive pacemaker	4. Peripheral arterial vascular disease history or suspicion of lower limb arterial insufficiency
5. Prediction of 2 to 12 days of ICU permanence	5. Signals of intracranial hypertension	5. Severe cardiovascular instability and/or use of vasoactive drugs in infusion ≥ 0.5 mcg/kg/min
6. Daily protein consumption standardized for the ICU medical and nutrition teams	6. Neoplasia in chemotherapy treatment	6. Deep coagulopathy (prothrombin time (PT) > 2.5 times the normative values, activated partial thromboplastin time (APTT) > 2 times the normal or platelet count ≤ 50.000/μl)
	7. Non-consolidated fractures	7. Heparin intravenous infusion ≥ 2 UI/ml
		8. Fever or hypothermia
		9. Anemia
		10. Neurodegenerative disease
		11. Musculoskeletal disease

*ICU* intensive care unit

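### Repeated interruption of training removes the patient from the study, not only from training, so later strength, function and quality-of-life outcomes are lost in patients selected by intolerance of their arm

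*Protocol article*

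**What the plan says.** The rule is in the protocol article under *Cardiovascular safety and applicability of peripheral muscle training*. After listing the physiological limits and signs that interrupt a session, it states that "two consecutive training attempts will be performed after the first training interruption before withdrawing the patient from the study". The sentence opens "Except for the occurrence of deep venous thrombosis", so a thrombosis gets no further attempts; the natural reading is that such a patient leaves at once.

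Two neighbouring statements show that leaving the study is meant. One reason given for the repeat attempts is "to maintain the training frequency in case the patient continues in the study". The outcome of failing them is described as follows: "In case of exclusion, the protocol will be considered unsafe for this patient".

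At arm level the section adds that "in case 15% or more unsafe conditions occur in the same training protocol, the protocol will be excluded from the study".

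The *Secondary objective* is to "investigate the effects of this intervention on neuromuscular adaptations, physical function, and quality of life of ICU coma-surviving patients". Strength is measured by the "Medical Research Council (MRC) score after 12 h of T2, in the ICU and at hospital discharge". PFIT follows the same timing (*Physical function adaptations*). Barthel and SF-36 are repeated by telephone 6 and 12 months after hospital discharge. Muscle thickness and echo intensity are scanned daily up to 12 h after the last session.

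**The concern.** Stopping an intervention and stopping observation are different decisions, and the rule merges them. The trigger is the patient's reaction while undergoing the assigned protocol. It therefore occurs after randomisation and may occur at different rates in PM, BFRp and BFRpE. The patients still observed in each arm would then be those who tolerated that arm, and the arms would no longer be comparable as randomised on the secondary outcomes.

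There is also a safety cost. Follow-up ends for exactly those patients for whom the training was declared unsafe, in a study whose primary objective is cardiovascular safety.

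A later analysis plan cannot repair this. It can define an analysis set of all randomised patients, but it cannot supply measurements that were never taken.

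**Working it through.** **Inputs.** Total of 39 patients, base of 30, planned loss of 10% per group (*Sample size rationale*); three arms; 15% closure rule and 5% thrombosis rule (*Cardiovascular safety and applicability*). Equal allocation is assumed, giving 39/3 = 13 per arm. The article gives no expected withdrawal rate, so there is no figure of the plan to reproduce on this point. Going from 10 to 13 per arm does not match a 10% allowance (3/13 = 23.1%), but that is a separate matter and nothing below depends on it.

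**Step 1: is continued assessment promised anywhere?** The only provision for incomplete data is in the *Discussion*, where the last daily assessment may be used after unexpected discharge or death. Safety withdrawal is not mentioned there. *Statistical analysis* specifies a mixed model with group and time fixed and subject random, and does not address withdrawn patients.

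**Step 2: what falls after withdrawal?**

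| Outcome | Scheduled | Effect of withdrawal |
|---|---|---|
| MRC, PFIT | 12 h after T2, ICU and hospital discharge | lost completely |
| Barthel, SF-36 | 6 and 12 months | both follow-up values lost; baseline kept |
| Muscle thickness, echo intensity | daily, then 12 h after last session | only values after withdrawal lost; earlier scans can enter the mixed model |

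**Step 3: share of an arm.** Share = m/n for m withdrawals among n patients.
- n = 13: 1/13 = 7.7%; 2/13 = 15.4%.
- n = 10 (the base of 30 over three arms): 1/10 = 10%; 2/10 = 20%.

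If the 15% rule counts withdrawn patients over the arm size, the second withdrawal closes the arm at either size, so an arm that stays open can lose only one patient in this way. The text counts unsafe conditions and gives no denominator, so this cap is not assured.

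**Step 4: how likely is one withdrawal?** P(at least one of 13) = 1 − (1 − p)^13. The per-patient risk p is assumed, since the documents give none.
- p = 5%: 1 − 0.95^13 = 49%
- p = 10%: 1 − 0.90^13 = 75%
- p = 20%: 1 − 0.80^13 = 95%

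**Step 5: how far could an arm mean move?** If m of 13 patients are lost and their unobserved outcomes would have been g SD worse than those retained, the retained mean exceeds the full-arm mean by (m/13) × g. The gap g is assumed. With m = 1 and g from 0.5 to 2, the shift is 0.04 to 0.15 SD. This applies to the outcomes that are lost completely. It overstates the effect on muscle thickness, where earlier scans remain. MRC, PFIT and the telephone outcomes exist only in patients who wake and survive, so the number contributing may be below 13 and one loss would then weigh more.

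**The case against.** The strongest reply is that this is a pilot whose primary objectives are cardiovascular safety and applicability. For those objectives a withdrawn patient is not lost, because the withdrawal itself is recorded as an unsafe result. That stands, and it limits the severity. It does not remove the point, because the outcomes at risk make up the whole secondary objective.

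A second reply is that analysis in the randomised arm is commonly left to an analysis plan that is not shown. That is fair for the analysis set. It does not cover data collection, which the article fixes by its own wording.

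Several stronger readings are tempting but not supported:

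- **That the loss favours BFRp and BFRpE.** PM has no cuff or stimulator, and the *Background* calls the cardiovascular effects of cuff release unknown, so unequal loss is plausible. But the limits apply to PM too. They include a diastolic pressure above 80 mmHg, while *Peripheral muscle training* lets a session start with any value between 60 and 100. Those two statements must be reconciled. As they stand, interruptions can arise in any arm from the patient's starting state.
- **That muscle data disappear as well.** Nothing says that earlier scans are discarded, and the mixed model can use them.
- **That two or three withdrawals shift a surviving arm.** This conflicts with reading the 15% rule as withdrawn patients over 13. Similarly, if the 5% thrombosis rule is counted per arm, one thrombosis (1/13 = 7.7%) already makes that protocol unsafe and impracticable.
- **That closing an arm removes its patients or data.** The text excludes the training protocol. It does not say what happens to patients already in that arm.
- **That fever or anaemia arising after randomisation ends participation.** *Study population* says "All the criteria will be reevaluated before each training session, according to the clinical specificity of the criteria". This may only decide whether a given session goes ahead.

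**Conclusion.** The point holds as a stated rule with a foreseeable consequence: study withdrawal is tied to intolerance of the assigned training, and no provision for continued assessment is given. The effect is selective loss of MRC, PFIT and 6- and 12-month Barthel and SF-36, together with truncated muscle series. Its size is one patient, or 7.7% of an arm, per withdrawal under equal arms of 13. The shift of 0.04 to 0.15 SD in an arm mean is an illustration that rests on an assumed gap between withdrawn and retained patients, not an estimate. Neither the frequency of withdrawal nor the direction of the bias can be derived from the article.

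Severity is moderate, because the harm is confined to secondary outcomes of a pilot. It still merits correction: the *Abstract* says these data will inform the design and sample size of a later trial, so an estimate from tolerant patients only would be carried forward. Classification: cheap improvement.

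**What to change.** Leave the interruption rules and thresholds as they are. In *Cardiovascular safety and applicability of peripheral muscle training*, replace withdrawal from the study by discontinuation of the training protocol. Then add that patients who discontinue training for safety, including after thrombosis, and patients of any arm closed under the 15% rule:

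1. keep all remaining scheduled ultrasound, MRC, PFIT, Barthel and SF-36 assessments where consent allows;
2. are analysed in the arm to which they were randomised.

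Because T2 is tied to the last training session, say which time point anchors the post-training assessments in patients who stop early. State also the numerator and denominator of the 15% rule, so that its effect on an arm can be foreseen.

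**Cost.** A wording amendment, plus some additional bedside scans and telephone calls. Effect estimates will include patients who received little training, which dilutes any effect of the training as delivered. *Trial status* reports recruitment suspended with too few participants, so on the article's account the change can still be made before most patients are enrolled or followed up.

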## Methods

### Primary objectives

The primary objectives are to investigate the effect of BFRp and BFRpE on cardiovascular safety in comatose patients in the ICU and to investigate the applicability of such protocols as early motor intervention methods in intensive care.

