### Study interventions

#### Peripheral muscle training

After T1, in view of the cardiovascular safety and applicability of PM, BFRp, and BFRpE, training sessions will be held twice a day, divided by 4 h [51]. The starting training leg will be randomly chosen at T1 and, from that, alternated in every training session. Patients will undergo the experimental protocol if they present controlled temperature (between 36.5 and 37.5 °C), stable blood pressure (> 100 and < 150 of SBP and > 60 and < 100 of DBP), SpO_2_ > 90%, respiratory rate (RR) < 25 rpm, and HR > 60 and < 140 bpm [55].

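### No applicability trigger counts sessions that were due but not given, so a protocol that could seldom be delivered could still avoid being called impracticable

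*Protocol article*

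**What the plan says.** Primary objectives: alongside cardiovascular safety, the trial is "to investigate the applicability of such protocols as early motor intervention methods in intensive care".

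Cardiovascular safety and applicability of peripheral muscle training gives the decision rules. "To evaluate the applicability, the number of adverse events and intercurrence will be recorded", and a protocol fails "if a total number of adverse events and/or intercurrence overcome 20% of the total training sessions", or if "there is deep venous thrombosis occurrence in at least 5% of the patients, protocols will be considered unsafe and impracticable". A further sentence reads: "If cardiovascular variations are greater than 20% of the baseline, the protocol will be considered impractical". The same section drops a protocol from the study once unsafe conditions reach 15%.

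Peripheral muscle training sets the schedule, "training sessions will be held twice a day, divided by 4 h", and makes it conditional: "Patients will undergo the experimental protocol if they present controlled temperature (between 36.5 and 37.5 °C"), followed by limits on systolic and diastolic pressure, oxygen saturation, respiratory rate and heart rate. Study population adds: "All the criteria will be reevaluated before each training session".

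The article does not say whether the total in the 20% rule means sessions due, started or completed. It does not define intercurrence.

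**The concern.** Whether an intervention is applicable in intensive care depends partly on whether it can be given as scheduled. The design itself expects that some sessions may not go ahead, since it checks vital signs and eligibility before each one. Yet every printed trigger responds to something that happens during or after training, or to a diagnosis in a patient. A session that never starts can set off none of them.

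At stake is the conclusion on a primary objective. The Abstract says the results will help plan a later trial. A finding that a protocol is practicable, reached without regard to how much of it was given, would be a weak basis for that planning.

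**Working it through.** The 20% limit is a fixed threshold with no derivation, so there is no figure to reproduce. I take the rule as written, across all sessions.

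**Step 1: does a blocked session enter each trigger?**
- Events or intercurrence above 20% of sessions: a session not started yields no training event. If the denominator is sessions held, it drops out of both parts of the ratio. If the denominator is sessions due, it only enlarges the denominator.
- Deep venous thrombosis in at least 5% of patients: counted per patient, so the number of missed sessions does not enter.
- Cardiovascular variation above 20% of baseline: needs measurements from a session that took place.
- 15% unsafe conditions: follows from interrupted sessions and failed repeat attempts, so again needs sessions that were started.

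No trigger moves towards failure when sessions are blocked.

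**Step 2: sessions due per arm.** S = patients × 2 per day × days. Patients per arm are 39/3 = 13 as planned, or 30/3 = 10 before the allowance for losses (Sample size rationale). Predicted coma is 2 to 6 days (Table 1). S therefore runs from 10 × 2 × 2 = 40 to 13 × 2 × 6 = 156. The example below assumes 4 days: 13 × 2 × 4 = 104.

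**Step 3: insensitivity to delivery.** Let f be the share of due sessions started and r the event rate per started session. Neither is in the documents. Assume r = 5%, at most one event per session, and independent sessions.
- f = 1: all 104 sessions given. The rule needs more than 0.20 × 104 = 20.8 events, that is 21. The probability of tripping is 0.00.
- f = 0.10: 10 sessions given. With sessions held as denominator it needs more than 0.20 × 10 = 2 events, that is 3; for a binomial with n = 10 and probability 0.05 this has probability 0.01. With sessions due as denominator it needs 21 events from 10 sessions, which is impossible under these assumptions.

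The 20% rule gives nearly the same answer whether 104 or 10 sessions were delivered.

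**Step 4: the undefined denominator.** If it meant sessions due, the observed rate would be f × r and the rule would trip only when r > 20%/f:
- f = 0.90: 20/0.90 = 22.2%
- f = 0.75: 20/0.75 = 26.7%
- f = 0.50: 20/0.50 = 40%

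With r = 30% and f = 0.50 (52 of 104 started), the probability of tripping is 0.07 on sessions due (21 events needed) against 0.94 on sessions started (more than 10.4, so 11 needed). With f = 0.75 (78 started) it is 0.76 against 0.98. On the sessions-held reading this dilution does not arise and only the gap in Step 3 remains.

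**The case against.** A reader might infer that applicability is judged only by adverse events per session. That is too strong: the article also has the thrombosis, cardiovascular-variation and unsafe-condition rules, and the 20% rule includes intercurrence. These do not close the gap, for the reasons in Step 1.

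A reader might also infer that the event rate is diluted. The more natural reading of training sessions is sessions held, and on that reading it is not. The dilution figures apply only to the other reading.

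The article does not say that a failed start check cancels a session rather than delaying it, and it gives no delivery rate. One might infer from the narrow temperature window that many sessions will be lost. Nothing in the documents gives the distribution of temperature in eligible patients, and fever and hypothermia are themselves exclusion criteria, so no such rate can be derived.

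The start limits are common to all three arms, so a failed check reflects the patient's condition rather than intolerance of one protocol. That is fair for comparing arms. It does not settle whether a protocol can be delivered in this setting, which is part of the stated objective.

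Study population does provide for counting sessions, but to control the volume of stimulus, not to judge applicability. Intercurrence might be meant to include a session that could not start; it is undefined, and the Discussion uses it for events reported during training.

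Finally, a condensed article may leave session logs and adherence summaries to a fuller document. That would excuse silence. Here the decision rule for a primary objective is printed with its thresholds, and as printed it omits delivery.

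**Conclusion.** The point holds in a limited form. None of the printed triggers reflects due sessions that were not started or completed because the start limits or re-checked criteria were not met. A protocol that could seldom be delivered could therefore avoid being called impracticable. This conclusion rests on the text alone and needs no assumed rate.

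How often it would matter is unknown. The figures above depend on assumed values of f and r, a 4-day coma, at most one event per session, and independence between sessions, which repeated sessions in one patient are unlikely to satisfy exactly. They show how the rule behaves and do not forecast this trial. The documents do not show that sessions will be lost in large numbers, that the event rate is diluted on its natural reading, or that the next trial will assume an exposure that was not reached.

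**What to change.** 1. State that the 20% event rule uses sessions started as its denominator.
2. Report by arm the sessions started and the sessions completed, each over sessions due (two per day from T1 to waking, death or ICU discharge). Give the reason for each missed session and a 95% interval that allows for several sessions per patient. Say how a delayed session is counted.
3. Do not conclude that a protocol is applicable from the event rate alone. Judge the event rate jointly with the delivery proportion, against a criterion the investigators set in advance.

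The start limits and eligibility criteria are unchanged. The cost is a change of wording and one log line per due session; the pre-session checks are already part of the protocol. The applicability figure may turn out less favourable.
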